### Data collection and instruments: cost-effectiveness

The question that is central to the economic analysis is whether the WICM is cost-effective compared with traditional care. The outcome parameter used is cost per QALY (quality-adjusted life-year). For this, the EuroQol (EQ-6D) will be used to measure the quality of life of the elderly persons and will subsequently be converted into disability-adjusted life-years (DALYs). For the cost calculation, the volume of care will be linked to the actual, integral cost per medical service [60]. This will be used to make the instructions for cost research in economic evaluations [61]. Thus, the total care consumption of the elderly will be determined. The above-mentioned patient files, questionnaire, and time tracking form will provide insight into which care was received per elder, how much and from whom.

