### Data collection and instruments: frail elderly

Outcome data and data on demographics (age, sex, living arrangement, education, and marital status) will be collected with questionnaires and file research at three points in time: T0, T1 (3 months after inclusion), and T2 (12 months after inclusion). Research has shown that effects can be expected 3 months after starting to use the EASYcare instrument [41]. The T2 measurement takes place to determine long-term effects. All elderly will be visited at home by trained interviewers recruited from the region of Walcheren to ensure a cultural fit with the elder. Interviewers will have a background in healthcare to ensure a high-quality interview. Every elder will be given a gift at T1 as a token of appreciation and to motivate further participation. File research will occur at the GP practices. The following instruments will be used (see Table 1):

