##### EQ-6d

The EuroQol (EQ6D) is used to measure quality of life in terms of valued health and is composed of the dimensions mobility, self-care, usual activities, pain/discomfort, anxiety/depression, and cognitive functioning [45,46]. Each dimension is scored on three levels: ‘no problems,’ ‘some problems,’ and ‘severe problems.’ The EQ-6d will also be used to calculate cost-utilities of health care.

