## Abbreviations

WICM: Walcheren Integrated Care Model; GP: General practitioner; GFI: Groningen Frailty Indicator; SF-36: Short form (36) health survey; ICECAP: Index of capability for older people; EQ-6d: EuroQol (6 dimensions); SRB: Self-related burden; VAS: Visual analogue scale; CSI: Caregiver strain index; ASIS: Assessment of the Informal Care Situation; CSAI: Community Service Attitude Inventory; iBMG: Institute of Health Policy and Management; Qaly: Quality adjusted life years; Dalys: Disability adjusted life years; CQ-index: Consumer quality index.

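### The economic outcome is cost per QALY, but the article says the EQ-6D will be converted into DALYs, a different measure that does not give the denominator of that ratio

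*Protocol article*

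**What the plan says.** Four places in the protocol article bear on this.

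- **Data collection and instruments: cost-effectiveness, outcome.** "The outcome parameter used is cost per QALY (quality-adjusted life-year").
- **Same section, next sentence.** "For this, the EuroQol (EQ-6D) will be used to measure the quality of life of the elderly persons", and the result "will subsequently be converted into disability-adjusted life-years (DALYs"). The opening words tie this step to the cost-per-QALY outcome just named.
- **EQ-6d, under Quality of life (frail elderly).** The instrument "is used to measure quality of life in terms of valued health", and "The EQ-6d will also be used to calculate cost-utilities of health care".
- **Abbreviations.** The two measures are listed as separate terms: "Qaly: Quality adjusted life years; Dalys: Disability adjusted life years".

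Table 1 schedules the EQ-6d for the elderly at all three measurement points: "T0, T1 (3 months after inclusion), and T2 (12 months after inclusion"). The article mentions no disability weights, years of life lost, cost-per-DALY outcome, or step from DALYs back to QALYs.

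**The concern.** Two consecutive sentences name different health measures for one ratio. A QALY weights time by a preference-based utility and counts health gained. A DALY adds years lived with disability, scored with disability weights, to years of life lost, and counts health lost. The EQ-6D can be scored as a utility, which leads to QALYs. Reaching DALYs from it needs further inputs and assumptions, and the article names none.

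At stake is whether the economic result answers the question posed. The section asks whether the new model is cost-effective compared with traditional care and commits to expressing this per QALY. An analyst who follows the conversion sentence produces a quantity that is not the stated denominator and cannot be set beside other cost-per-QALY results. An analyst who follows the outcome sentence departs from the stated conversion. The text should not leave that choice until the data are in hand.

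**Working it through.** The article gives no utility, disability weight, cost or cost-effectiveness ratio, so there is no figure of its own to reproduce. The check is mainly a comparison of texts, followed by an illustration on assumed inputs.

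**Step 1. The texts side by side**

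| Place | Measure implied |
|---|---|
| Cost-effectiveness, outcome sentence | QALY |
| Cost-effectiveness, conversion sentence | DALY |
| EQ-6d section (valued health, cost-utility) | utility, hence QALY |
| Abbreviations | both, as distinct terms |

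The DALY is spelled out in full in the conversion sentence and again in the abbreviations, so this is not a misread letter or a fault of text extraction. Nothing elsewhere in the article bridges the two measures.

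**Step 2. Does the conversion yield the stated denominator?**

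Assumed utilities at 0, 3 and 12 months:

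- experimental: 0.60, 0.66, 0.68
- control: 0.60, 0.60, 0.60

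Assumed extra cost: 1,000.

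QALYs over one year as area under the curve: (u0 + u3)/2 × 0.25 + (u3 + u12)/2 × 0.75.

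- Experimental: 0.63 × 0.25 + 0.67 × 0.75 = 0.1575 + 0.5025 = 0.66
- Control: 0.60 × 0.25 + 0.60 × 0.75 = 0.60
- Difference: +0.06 QALY
- Ratio: 1,000 / 0.06 = 16,667 per QALY gained

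For the disability part of a DALY, assume a weight of k × (1 − utility). With no deaths, the loss averted is k × 0.06.

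| k (assumed) | DALYs averted | Cost per DALY averted |
|---|---|---|
| 0.5 | 0.030 | 33,333 |
| 0.75 | 0.045 | 22,222 |
| 1 | 0.060 | 16,667 |
| 1.25 | 0.075 | 13,333 |

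The two ratios agree in size only at k = 1, that is, when the disability weight is exactly 1 minus the utility. The article does not say so.

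**Step 3. Deaths**

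Take a death at month 6 in a person with an assumed utility of 0.6.

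- QALY loss within the 12 months: 0.6 × 0.5 = 0.30.
- DALY loss if life lost is counted only to month 12 and k = 1: 0.5 year of life lost, less the disability the person would otherwise have had, 0.4 × 0.5 = 0.20. This leaves 0.30, the same as the QALY loss.
- DALY loss if life lost is counted over remaining life expectancy, assumed to be 5 to 10 years: 5 to 10 years of life lost.

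The two measures therefore coincide only under particular conventions for both the weights and the years of life lost. Neither convention is given.

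**The case against.** The strongest reply is that this is one wrong word. The outcome sentence names the denominator plainly, the conversion sentence serves it, and the EQ-6d section points to utilities. QALYs are the natural reading, and most health economists would compute them without hesitation. This is probably right about intent, and it limits the severity. It does not make the sentence correct: the article states a conversion target, and that target conflicts with its own outcome. Nor is this detail left to a fuller plan, since the step is stated rather than omitted.

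A reader might infer more than the text supports. Four such inferences should be set aside.

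- **That the denominator is undefined.** It is named as the QALY; what is wrong is the stated route to it.
- **That the abbreviation list shows a planned DALY analysis.** Such a list repeats terms from the body, and DALYs occur in the body only in this section. The entry rules out a typing error in the letters and is not independent evidence of intent.
- **That the opposite direction of the scales would make a better strategy look worse.** The sign changes only if cost is divided by a raw DALY difference. Expressed per DALY averted, as in the table above, a benefit is positive. A costlier, more effective strategy, as in the illustration, is also not a case of dominance.
- **That deaths would be dropped because only survivors are converted.** The article says nothing of the kind. Mortality appears in the power section only as one reason for loss to follow-up. How deaths enter the calculation is detail that a condensed article may leave out.

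**Conclusion.** The point stands as an error in the methods text, limited to the economic analysis. As written, the EQ-6D conversion produces DALYs, the outcome is cost per QALY, and nothing in the article connects them. The contradiction rests on the wording alone and needs no assumption.

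Its numerical size cannot be taken from the article. The range of 13,333 to 33,333 per DALY averted, against 16,667 per QALY gained, rests wholly on the assumed utilities, the assumed cost of 1,000 and the assumed k of 0.5 to 1.25. It shows only that the measures are not interchangeable.

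Severity is moderate. The power statement and the group comparisons of the primary quality-of-life measures, including the EQ-6d as an outcome in its own right, do not depend on this sentence. Under the QALY reading the planned EQ-6D data collection is unchanged.

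**What to change.** In the cost-effectiveness section, replace the DALY clause with a statement that EQ-6D states at T0, T1 and T2 will be converted into utilities and then into QALYs. Delete DALYs from that section and from the abbreviations. This agrees with the stated outcome and with the EQ-6d section.

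If DALYs were truly intended, change the outcome to cost per DALY averted, state the disability weights and how years of life lost are counted, and reconcile the EQ-6d section with that choice.

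The first option costs one sentence and one abbreviation entry. It needs no new data, because the EQ-6D is already scheduled at all three time points, and it can be made at any time before the economic analysis. The same edit could also say how deaths enter the QALY calculation and whether the comparison is adjusted for T0 utility. Both are optional detail, and their absence from the article is not an error.

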### Data collection and instruments: process indicators

To determine the level of coordination, coherence, and satisfaction with care processes, the following process indicators will be measured with questionnaires, file research, interviews, diaries, and focus groups (see Table 4).

#### Degree of integration

##### Questionnaire

To determine the degree of coherence, continuity, and co-operation, a questionnaire will be developed based on a systematic review of integration indicators and instruments for measuring integration. The questions will be part of the questionnaire sent to the health professionals as described above. Health professionals are again asked to assess the current levels of integration and those 18 months previously.

#### Health professionals’ experiences with the quality and process of care

##### Questionnaire

Questions on satisfaction with the process of care and level of integration will be derived from the above-mentioned results of the systematic review.

##### Relational coordination survey for patient care

The quality of the relationships and communications between health professionals will be measured with the relational coordination survey for patient care, an instrument covering the following dimensions: shared goals, knowledge and respect, frequency and timing of communication, and problem-solving orientation of the communication [62,63].

##### Diaries

The geriatric nurse practitioner and secondary line geriatric nursing specialist will be asked to keep a diary of their experience with the WICM. Every 3 months, a researcher will briefly interview the geriatric nurses over the telephone to discuss their experiences based on the diary.

##### Interviews

After the completion of the experiment, interviews will be held with involved professionals. Discussions will cover their experience with the WICM, conducive and non-conducive factors that played a role and any adjustments that the model may require.

##### Focus groups

For both the experimental and control regions, 3 focus groups will be organized for the health professionals and patient organizations involved. These focus groups will be used to gain insight into satisfaction with the model and its integration. The groups will also strengthen the analysis by reflecting on the results of the study.

The frail elderly and caregiver experiences with the quality and process of care.

##### Consumer quality index (CQ-index)

The CQ-index, a Dutch standardized method for measuring experiences of patients/clients with health care, will be used. Covered domains are quality of the health professionals, information, participation, treatment, communication, and received care [64,65]. CQ-questionnaires are developed for different types of care. The CQ-questionnaire for home care will be used as a reference point and be completed with questions on the coherence and coordination of care. Elderly will be asked at T0, T1, and T2 regarding their experience of the care and care processes. Caregivers will be asked at T0, T1, and T2 regarding their experiences of the care given to their elder and the care and attention that they receive from health professionals.

### Data analysis

The experimental and control groups will be described at every point in time with descriptive statistics. Similarity of characteristics between the two groups will be assessed with t-tests, chi-square tests, and Fisher’s exact tests. Bivariate analyses and regressions with the demographic characteristics will determine multicollinearity and correlations with the process and outcome measures. All analyses will be controlled for differences in baseline characteristics and demographic characteristics. For the self-constructed questionnaires, factor analyses and reliability analyses will be performed to determine construct validity. To determine changes over time, t-tests will be performed for each process and outcome measure. For each measure, regression analyses will be performed with the T2-score as the dependent variable and the T0-score, the research group (experimental or control), and demographic variables as independent variables. With subgroup analyses, potential variation between study results between subgroups will be analyzed.

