### Study design

The study has a quasi-experimental design in which the effects will be measured before and after the study. A control group will also be used. The study includes an evaluation of process and outcome measures for the frail elderly, their caregivers, and health professionals, as well as a cost-effectiveness analysis. To evaluate the effects, a combination of qualitative and quantitative research methods will be used. (See Tables 1, 2, 3 and 4). The study protocol has been reviewed by the medical ethics committee of the Erasmus Medical Centre, Rotterdam, the Netherlands, under protocol number MEC-2013-058. They waived further examination as the rules laid down in the Medical Research Involving Human Subjects Act did not apply.

**Table 1 T1:** Outcome measures and data collection frail elderly

**Outcome and instrument**	**Method**	**Data collection time**		
		**T0**	**T1**	**T2**
*Primary outcomes*				

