### Power calculation

We will include 220 elderly in both the experimental and control group. We expect a 10% loss to follow-up (due to mortality, re-housing, impossibility or unwillingness to participate further) between inclusion and T1 and a 20% loss between T1 and T2. The sample is sufficient to detect changes in our primary measure of quality of life. Assuming an average effect size of 0.5 and significance of 5%, this gives a power of 0.997. If we assume a small effect size of 0.3 with a significance of 5%, this still supplies sufficient power at 0.837. Interfering variables will also play a role. At an average effect size (f2) of 0.15 and significance of 5%, assuming five independent variables, the power is 0.97. Even with 15 independent variables, the power remains sufficient at 0.856.

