### Study sample: sampling and eligibility criteria

Sampling will take place at GP practices in Walcheren. The experimental group will consist of the elderly patients of 8 GPs from 3 GP practices located in the east of Walcheren who will provide care according to the WICM. The control group will consist of 6 GPs from 5 GP practices in the north, south, and west of Walcheren who will provide traditional care. All elderly aged 75+ years in these practices who live independently will be asked to complete the GFI, along with several demographic questions and a consent form. Approximately 900 elderly in both the experimental and control practices will be contacted. The questionnaire is accompanied by a letter from the GP to raise the likelihood of response and assure that the elderly are well informed. After being sent a reminder, the elderly will be contacted by telephone or visited at home to be asked to participate and to help complete the questionnaire if necessary. These activities are expected to result in an 80% response rate. Elderly will be included if they score ≥4 on the GFI, if they have signed the consent form, or if they are able to make that decision themselves. Exclusion criteria are as follows: elderly on a waiting list for a nursing home, elderly who are not able to decide themselves if they want to participate (e.g., in case of dementia), and elderly with a life expectancy of <6 months due to a terminal illness. Included elderly will be asked to provide contact information for their informal caregiver. The caregivers will be contacted either by telephone or face-to-face during the first visit from the researchers at the home of the elderly subjects. They will be asked to fill in a written consent form if they agree to participate. Non-respondents will be contacted again by telephone. A response rate of 60% is expected. Health professionals will be selected based on their function and region of employment. An estimated 400 questionnaires will be sent to health professionals in the experimental and control groups. We expect a response rate of 50%.

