### Evaluation study

The choice for a quasi-experimental design instead of a randomized control trial may seem suboptimal to some. However, in many studies on organizational change, randomization is impractical, impossible or even undesirable [69]. This is the case in our study as health professionals cannot give traditional care and care according to the model at the same time. Blinding is impossible. For the elderly, it is undesirable to receive care from a different GP or organization from one previously used.

However, choosing for a quasi-experimental design presents our study with some challenges. The absence of randomization makes results subject to contamination by confounding variables [70]. Potentially confounding variables have been accurately defined based on literature, experiences of health professionals and comparable studies. Inclusion and exclusion criteria are set. However, there is no guarantee that some confounding variables will be missed. It is also conceivable that differences found in the experimental group are not the result of the intervention but of the additional attention given by both health professionals and interviewers [71]. It is debatable if this “Hawthorne-effect” is really problematic because increased and patient-centered attention for the frail elderly is one of the goals of the model. Irrespective of the design chosen, the biggest potential obstacle is the willingness of the elderly and their caregivers to participate in this study over the longer term. To increase willingness, a request to participate will be sent, as described above, via the elders’ own GPs, interviewers will be from the region and gifts will be given.

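### In a non-randomised comparison of regions, neither the named regression nor the general adjustment sentence secures adjustment for baseline frailty (GFI), although every included person has a GFI score

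*Protocol article*

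**What the plan says.** All references are to the Protocol article.

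- **Design.** Under Study design: "The study has a quasi-experimental design in which the effects will be measured before and after the study". A control group is used, and groups follow geography. Under Study sample: "The experimental group will consist of the elderly patients of 8 GPs from 3 GP practices located in the east of Walcheren". The controls are patients of 6 GPs in 5 practices in the north, south and west.
- **Comparison of groups.** Under Data analysis: "Similarity of characteristics between the two groups will be assessed with t-tests, chi-square tests", with Fisher's exact test as a third tool.
- **General adjustment sentence.** Same section: "All analyses will be controlled for differences in baseline characteristics and demographic characteristics".
- **Named model.** Same section: for each measure, the T2-score is regressed on the T0-score, the research group and demographic variables. The demographics are listed under Data collection and instruments: frail elderly: "Outcome data and data on demographics (age, sex, living arrangement, education, and marital status) will be collected".
- **Frailty score.** The GFI is requested from all independently living patients aged 75 or over in both groups' practices (Study sample). A score of at least 4 is needed for inclusion, on a scale of 0 to 15 (description of the intervention).
- **Source of confounders.** Under Evaluation study in the Discussion: "Potentially confounding variables have been accurately defined based on literature, experiences of health professionals and comparable studies". The article does not list them.

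**The concern.** Without randomisation, covariate adjustment is the main analytic protection against confounding, and the Evaluation study section itself recognises that threat. Frailty is the obvious candidate. It defines the study population, it covers physical, cognitive, social and psychological functioning, and it is likely to predict quality of life and function a year later. The entry threshold of 4 truncates its range but does not equalise it, so the two sets of practices may differ in how frail their included patients are.

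The plan makes two statements about adjustment. The named model has no place for GFI. The general sentence leaves room for it, but on its wording only where a difference is seen. A non-significant baseline comparison does not show that confounding is absent, so a moderate imbalance could go unadjusted. At stake is a bias in the group effect, in either direction, that the T0-score and demographics do not fully remove.

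**Working it through.** **1. The plan's own regression power.** The inputs under Power calculation are f² = 0.15, 5% significance, and 5 or 15 independent variables. The sample starts from "We will include 220 elderly in both the experimental and control group" with 10% loss to T1 and then 20% to T2. Adding the losses gives 220 × 0.70 = 154. For the overall F test with u predictors, v = N − u − 1 and noncentrality λ = f² × N = 0.15 × 154 = 23.1:

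| Predictors | Power, N = 154 | Stated |
|---|---|---|
| 5 | 0.971 | 0.97 |
| 15 | 0.856 | 0.856 |

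Both stated figures reproduce at N = 154.

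**2. Cost of extra covariates in the same set-up.** One more predictor moves 0.971 to 0.962 (6) and 0.856 to 0.843 (16). Two more move 0.971 to 0.952 (7). With both groups in the regression (N = 308), power with 7 predictors is above 0.999. The power calculation gives no reason to leave GFI out.

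**3. Assumptions for the bias.** The document gives neither figure:
- GFI imbalance between groups: 0.2 SD.
- Partial slope of the T2-score on GFI, given T0-score and demographics: 0.2 to 0.4 SD per SD.

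The imbalance that matters is the part left after T0-score and demographics. The raw 0.2 SD is used in its place.

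**4. Case A: GFI is never adjusted for (the named model read literally).**
Bias = imbalance × slope
- 0.2 × 0.2 = 0.04 SD; 0.04 / 0.3 = 13%
- 0.2 × 0.4 = 0.08 SD; 0.08 / 0.3 = 27%

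The denominator 0.3 is the small effect size in the plan. With 158 per group (220 × 0.9 × 0.8, compounding the losses) and residual SD 1, the standard error is √(2/158) = 0.1125. The shift is 0.36 to 0.71 standard errors, and a two-sided 5% test then has a type I error of about 0.065 to 0.11.

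**5. Case B: GFI enters only if a two-sided 5% baseline test flags it.** At 220 per group, SE = √(2/220) = 0.0953 SD.
- Probability of flagging a true imbalance: 0.18 at 0.10 SD, 0.35 at 0.15 SD, 0.55 at 0.20 SD, 0.88 at 0.30 SD.
- Bias in the fitted effect follows the *observed* imbalance. An observed 0.2 SD gives z = 0.2 / 0.0953 = 2.10, p = 0.036, so it is flagged. The largest unflagged difference is 1.96 × 0.0953 = 0.187 SD.
- With a true imbalance of 0.2 SD, the test is silent 45% of the time. The mean observed imbalance in those cases (truncated normal) is 0.115 SD.
- Bias when unflagged: 0.115 × (0.2 to 0.4) = 0.023 to 0.046 SD, or 8 to 15% of 0.3.
- Averaged over flagged and unflagged cases, with zero bias once flagged: 0.445 × (0.023 to 0.046) = 0.010 to 0.021 SD, or 3 to 7% of 0.3.

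The cases are alternatives. The 13 to 27% belongs to Case A, where the test plays no part. The detection probabilities belong to Case B, where the bias is smaller.

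**The case against.** The strongest reply has four parts.

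- **No selection rule is stated.** A reader might infer that covariates are chosen by p-value. The document does not say so: the tests and the adjustment sentence stand near each other, with no threshold or selection step between them. The Evaluation study section gives other sources, namely literature, professional experience and comparable studies. This objection stands. What remains is that no other means of recognising a baseline difference is named, and Data analysis does not tie the model to those predefined confounders.
- **The adjustment is not closed.** A reader might infer that the analysis adjusts only for T0-score and demographics. The general sentence covers all analyses and is wider, so GFI could come in that way. This also stands: GFI is not shut out, but its inclusion is not secured. Nor would between-group tests make the covariate set change from one outcome to the next, because their results do not depend on the outcome modelled.
- **The effect may be small.** The T0-score of each outcome carries part of frailty's influence, entry at 4 or more narrows the range, and the imbalance and slope are assumed. This limits the size of the concern. It does not remove it, since several outcomes are single items (the social functioning question and Cantril's ladder, for example) and are unlikely to capture multi-domain frailty fully.
- **This is an article.** A complete confounder list may sit in a fuller document, and its absence here is no fault. The point rests instead on the model that the article does specify, which omits a prognostic variable already held for every included person.

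**Conclusion.** The concern holds in a limited form. The named regression leaves out baseline GFI, and the general sentence would admit it only if a baseline difference is seen, so adjustment for frailty is not assured in a design that depends on adjustment.

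Under the assumed 0.2 SD imbalance and 0.2 to 0.4 slope, the bias is 0.04 to 0.08 SD if GFI is never in the model. If a 5% baseline test decides, it is about 0.01 to 0.02 SD on average and 0.02 to 0.05 SD when the test is silent. These figures are illustrative and probably on the high side, because the T0-score takes up part of the effect. The document does not support the stronger conclusion that a 13 to 27% distortion arises from test-driven selection. The point is worth acting on because the remedy is nearly free.

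**What to change.** Replace the two adjustment statements under Data analysis with one covariate set, fixed in advance and used in every elderly outcome model whatever the baseline p-values:

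- T0-score of the outcome;
- age, sex, living arrangement, education and marital status;
- baseline GFI score;
- baseline Katz-15, except where Katz-15 is the outcome, since its T0-score is then already in the model.

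If the predefined confounders mentioned in the Discussion include others, name them in the same sentence.

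**Cost.** A change of wording, one or two degrees of freedom and no new data: GFI is needed for entry and Katz-15 is already collected at T0. In the plan's own set-up (N = 154), two extra covariates lower power from 0.971 to 0.952.

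Reporting standardised differences in place of baseline p-values, and a propensity-weighted sensitivity analysis on the same variables, are optional. Neither they nor the added covariates would deal with unmeasured differences between the regions.

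### Whole GP practices are allocated (3 versus 5), but the power figures and the T2 regression treat the elderly as independent; any positive residual intracluster correlation makes the standard error too small and the power too high

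*Protocol article*

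**What the plan says.** The sampling section of the protocol article forms the two groups from whole practices. It states "The experimental group will consist of the elderly patients of 8 GPs from 3 GP practices located in the east of Walcheren" and "The control group will consist of 6 GPs from 5 GP practices in the north, south, and west of Walcheren". The Evaluation study part of the Discussion gives the reason: a professional cannot deliver both kinds of care at the same time.

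The Power calculation section starts from numbers of elderly persons: "We will include 220 elderly in both the experimental and control group". It allows for attrition ("We expect a 10% loss to follow-up" up to T1, then "a 20% loss between T1 and T2") and reports "Assuming an average effect size of 0.5 and significance of 5%, this gives a power of 0.997" and "If we assume a small effect size of 0.3 with a significance of 5%, this still supplies sufficient power at 0.837". It adds two regression powers, 0.97 with five predictors and 0.856 with fifteen. The number of practices, an ICC and a design effect do not enter.

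The Data analysis section fixes one form of model for all outcomes: "regression analyses will be performed with the T2-score as the dependent variable and the T0-score, the research group (experimental or control), and demographic variables". Practice and GP are not among the terms. Clustering is not mentioned anywhere in the article.

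**The concern.** Everyone in a practice is in the same arm, and the model of care works through the practice. The GP and a practice-based nurse screen and assign cases, the GP leads the multidisciplinary meeting, and the practice is the single entry point. Outcomes of elderly persons in one practice may therefore resemble each other. The comparison rests on 8 practices (14 GPs), not on several hundred independent persons.

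A regression that ignores this computes the standard error of the group coefficient as if every person were a separate allocation. Ordinary variation between practices can then be declared an effect of the care model. This applies to the group effect on every outcome of the elderly, including the primary quality-of-life measures.

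**Working it through.** **Inputs.** From the protocol: 220 per arm; losses of 10% and 20%; effect sizes 0.5 and 0.3; significance 5%, sidedness not stated; 3 practices (8 GPs) against 5 practices (6 GPs). Assumed: ICC of 0.01, 0.02 or 0.05, because the documents give none, and practices of equal size within each arm.

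**1. Reproduce the plan's figures.** Adding the losses leaves 220 × 0.70 = 154 per arm. (Taken in sequence, 220 × 0.9 × 0.8 = 158.) With independent observations, the two-sample t-test at n = 154 per arm gives:

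- one-sided 5%: 0.997 at d = 0.5 and 0.837 at d = 0.3, which are the stated figures;
- two-sided 5%: 0.992 and 0.747.

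With n = 158 the one-sided power at d = 0.3 is 0.845, and with n = 220 it is 0.933, so neither matches. The regression powers reproduce at N = 154 in total (0.971 and 0.856), again with no cluster term. The stated powers are therefore independent-observation figures, and 0.837 holds only one-sided.

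**2. Design effects by practice.** DE = 1 + (m − 1) × ICC, with m = 154/3 = 51.3 in the experimental arm and 154/5 = 30.8 in the control arm. The ratio of the true to the naive standard error is r = √[(DE₁ + DE₂)/2]. The true error of a nominal two-sided 5% test is 2 × [1 − Φ(1.96/r)].

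For ICC 0.02: DE₁ = 1 + 50.3 × 0.02 = 2.01, DE₂ = 1 + 29.8 × 0.02 = 1.60, and r = √1.80 = 1.34. The last column repeats the calculation by GP, with m = 154/8 and 154/6.

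| ICC | DE₁ | DE₂ | r | True error, by practice | True error, by GP |
|---|---|---|---|---|---|
| 0.01 | 1.50 | 1.30 | 1.18 | 9.8% | 7.5% |
| 0.02 | 2.01 | 1.60 | 1.34 | 14.4% | 10.1% |
| 0.05 | 3.52 | 2.49 | 1.73 | 25.8% | 17.3% |

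**3. Power by practice.** Normal approximation: Φ(d/SE − z), with SE = √[(DE₁ + DE₂)/154]. The figures in brackets use the noncentral t with 3 + 5 − 2 = 6 degrees of freedom.

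| ICC | d = 0.3, one-sided | d = 0.5, one-sided | d = 0.3, two-sided |
|---|---|---|---|
| 0 | 0.84 (0.75) | 0.997 (0.99) | 0.75 (0.60) |
| 0.01 | 0.72 (0.63) | 0.98 (0.95) | 0.60 (0.46) |
| 0.02 | 0.62 (0.54) | 0.95 (0.89) | 0.50 (0.38) |
| 0.05 | 0.45 (0.38) | 0.81 (0.72) | 0.33 (0.25) |

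With clustering by GP, one-sided power at d = 0.3 is 0.77, 0.71 and 0.57 at the three ICCs (normal approximation).

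**The case against.** **No ICC is given, and the model adjusts for baseline.** This stands as a limit on size. Adjustment for the T0-score may lower the residual ICC, and it lowers the residual variance. Suppose a T0–T2 correlation of 0.5 (an assumption), so that the residual variance is 1 − 0.5² = 0.75 of the total, and keep the same ICCs on the residual scale. Two-sided power at d = 0.3 is then about 0.73 at ICC 0.01 and 0.62 at 0.02. Without clustering the same adjustment would give Φ(0.3/√(0.75 × 2/154) − 1.96) = Φ(1.08) = 0.86, so a loss from clustering remains.

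**The GP may be the relevant cluster.** The abstract describes the groups by GP. The inflation is then milder, as the table shows, but it does not vanish.

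**A reader might infer that the plan has no usable power.** The figures do not support that. At d = 0.5 one-sided power stays at 0.81 or more up to ICC 0.05 by the normal approximation, and at 0.72 with 6 degrees of freedom.

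**A reader might set the two-sided 0.60, 0.50 or 0.33 against the stated 0.837 and blame clustering for the whole gap.** The step from 0.837 to 0.75 is sidedness. Only the rest is clustering.

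**A reader might infer that unadjusted between-group t-tests on outcomes are planned.** The Data analysis section assigns t-tests to the similarity of group characteristics and to changes over time. It also says that all analyses will be controlled for baseline and demographic differences. No such outcome test is clearly planned.

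**The matter could be left to a fuller plan.** This does not stand. The article itself fixes the model terms and the power figures, and those figures reproduce without any cluster allowance.

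**Conclusion.** The plan is wrong as written on this point. Allocation is by practice, while the power calculation and the T2 regression count persons as independent. For any positive residual ICC, the standard error of the group effect is understated and the stated powers are not reached.

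The direction is certain once the ICC exceeds zero; the size rests on an assumed ICC and on 154 per arm at T2. Over ICCs of 0.01 to 0.05 by practice, the standard error is too small by a factor of 1.18 to 1.73. The loss of power matters most at d = 0.3. The inflated false-positive risk applies whatever the true effect size.

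A separate limit remains: all experimental practices lie in the east. Differences in area are confounding, a problem that the Evaluation study section acknowledges in general terms. Correcting the standard error does not remove it.

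**What to change.** - **Data analysis section:** account for practice in every between-group outcome model by a practice random intercept with Satterthwaite or Kenward-Roger degrees of freedom. Report a practice-level analysis alongside, because with only 8 practices the practice variance is poorly estimated and may come out as zero. A GP-within-practice level need not be required: 6 GPs in 5 control practices leave almost nothing from which to estimate it.
- **Power calculation section:** restate power with the design effect over an ICC range, for example 0.01 to 0.05, for both effect sizes, and state whether the test is one- or two-sided.
- **Conclusions:** say that 3 practices are compared with 5, and that this model cannot separate area (east versus elsewhere) from the intervention.

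The cost is wider confidence intervals and lower stated power. No new data are needed, since participants are recruited through their practices.
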